**Erythrocyte and plasma separation**

Blood samples for erythrocyte and plasma selenoenzyme activity measurements will be transferred to EDTA coated blood tubes and centrifuged at 1210g at room temperature for 10 minutes. The plasma layer will be carefully removed and transferred to two 1.5mL cryovials for storage under liquid nitrogen. Isotonic saline (0.9%) solution will then be used to wash the remaining erythrocytes in the tube twice, using gentle tube inversion followed by centrifugation at 1210g at 4oC for 12 minutes. The erythrocytes will then be transferred to two 1.5mL cryovials and stored under liquid nitrogen.

**Determination of Protein Concentration**

Determination of the amount of protein in blood samples will be carried out using the dye binding assay of Bradford (1976) with a commercial source of human serum albumin (HSA) as the standard. The micro protein assay will be used; briefly 1mL of Bradford reagent will be added to 1mL of ~150 fold diluted sample and after 15 min the absorbance will be measured at 595 nm.

**Analysis of GPx1 activity**

GPx1 activity in blood samples (erythrocyte fraction) will be measured with hydrogen hydroperoxide as the substrate (Wendel 1981). The assay mixture will contain 25mM phosphate buffer pH 7.4, 2mM diaminoethanetetra-acetic acid (EDTA), 1mM sodium azide (NaN3), 3mM GSH, 0.2mM NADPH, 3U/ml yeast glutathione reductase, 0.1mM hydrogen peroxide and the appropriate amount of sample (e.g. 10mL). The reaction will be carried out at 37oC and oxidation of NADPH will be followed spectrophotometrically at 340nm.

**Analysis of glutathione peroxidase (GPx) activity**

GPx activity in blood samples will be measured essentially as described by Paglia and Valentine, 1967. All samples (erythrocytes, plasma and platelets) from one individual will be analysed in a single batch using a human reference serum sample (Seronorm) as an internal reference standard. Plasma samples will be added directly to the assay mixture without prior dilution whereas reconstituted erythrocytes (25L) will be diluted and incubated for 5 mins with 500L Drabkin’s reagent prior to addition to the assay. Platelet samples will be sonicated in ice-cold 50mM phosphate buffer pH 7.2 containing 4mM EDTA followed by centrifugation at 10000rpm, 4oC, the supernatant will then be diluted and treated with Drabkin’s reagent prior to assay. The reaction mixture will contain 1mM phosphate buffer pH 7.0, 0.01mM EDTA, 1U glutathione reductase, 5M glutathione, 0.25M NADPH, 2.5M tert-butyl hydroperoxide and 100L sample. The reaction will be carried out at 37oC and absorbance readings will be recorded at 340nm.

**Analysis of GPx4 activity**

GPx4 activity of blood samples will be determined using a sensitive and specific HPLC method as described by Bao et al., 1995. The substrate, 1-palmitoyl-2-(13-hydroperoxy-cis-9,trans-11-octadecadienoyl)-L-3-phosphatidylcholine (PLPC-OOH) will be prepared from PLPC using soybean lipoxidase as described by Maiorino et al., 1990. Briefly, PLPC-OOH will be separated from unoxidised phospholipid by FPLC on a PepRPC HR10/10 column with a gradient of water (100%) to methanol (100%). The concentration of the phospholipid hydroperoxide collected in 100% methanol will be determined by absorbance at 232 nm ( = 25,000 M-1 cm-1) (Chan, 1984). 1-palmitoyl-2-(13-hydroxy-*cis*-9, *trans*-11-octadecadienoyl)-L-3-phos-phatidylcholine (PLPC-OH) standards will be prepared as described by Bao et al., 1995.

The GPx4 activity assay mixture will contain 0.1M Tris-HCl, pH 7.4, 2mM diaminoethanetetra-acetic acid (EDTA), 1mM sodium azide (NaN3), 3mM GSH, 0.12 % Triton X-100, 25mM PLPC-OOH and the appropriate amount of plasma (e.g. 10 mL) in a final volume of 0.5mL. The reaction will be carried out at 37oC for approximately 20 min and termination achieved by the addition of ice-cold acetonitrile. Prior to HPLC analysis the samples will be centrifuged at 11,600 g for 2 min. An Ultracarb 5 ODS (20) column(250  4.6 mm) or other suitable C18 column will used to separate PLPC-OOH and PLPC-OH with a mobile phase of acetonitrile, methanol and water (50:49.5:0.5, by vol.) containing 10mM choline chloride. The flow rate will be maintained at 0.5mL/min and detection at 232 nm. Conversion of substrate to product will be determined from the peak height of PLPC-OH standards.

**Analysis of thioredoxin reductase (TrxR) activity**

TrxR activity in plasma will be measured as described by Holmgren & Bjornstedt (1995) using insulin as the substrate. The TrxR assay mixture will contain 80M HEPES pH 7.6, 3mM EDTA, 0.7M NADPH, 0.4M insulin, 30mM Trx and 70µL plasma (diluted 1:5 in water). The reaction will be incubated at 37oC for approx 20 min and then stopped with 1mM 5,5’-dithiobis-nitrobenzoic acid/6M guanidine hydrochloride in 0.2M Tris–HCl (pH 8.0), the absorbance will be recorded at 412nm. The absorbanceof the control (all assay components except Trx) will be subtracted from the absorbance of the sample andTrxR activity will be calculated based on the standard curve preparedusing pure TrxR.

**Determination of key Se-responsive protein levels**

Key Se-responsive protein levels will be analysed using appropriate proteomic techniques and using Western blotting techniques. Proteins from blood will be separated from blood using sodium-dodecyl sulphate polyacrylamide gel electrophoresis (SDS-PAGE) on a 12% NuPAGE Novex Bis-Tris gel (Invitrogen) and transferred to PVDF membrane (Millipore) following the manufacturer’s instructions. The membrane will be saturated for 1 hour at room temperature with Starting Block (TBS) blocking buffer (Pierce). Primary antibodies specific to Selenoprotein W1, Selenoprotein P and other key Se-responsive proteins will be used separately to probe the membrane, followed by a secondary horseradish peroxidase antirabbit IgG (Sigma). Protein bands will be visualised using chemoluminescence with a Supersignal West Pico Chemiluminescent substrate kit (Pierce) on a Fluor-S MultiImager (BioRad).

**RNA isolation from blood samples**

RNA will be extracted from whole blood and lymphocytes. For whole blood total RNA will be isolated using Tri Reagent BD (Molecular Research Centre) following manufacturer’s protocol. Lyphocytes will be isolated by diluting whole blood with 1 volume of phosphate buffered saline (PBS). Then a layer of 2 volumes of diluted blood will be placed on to 1 volume of Lymphoprep (Nycomed, UK) and centrifuged at 200g for 20 minutes at room temperature. The lymphocyte layer is removed and diluted >2 fold with PBS and centrifuged at room temperate for another 20 minutes at 200g. The supernatant is decanted off the remaining cell pellet. Total RNA is then extracted from the cells (after homogenization with a QIAshredder column) using Qiagen RNeasy mini kit according to the protocol described by the manufacturer (Qiagen, UK). RNA will be eluted from the column with RNase-free water and RNase inhibitor added immediately (20 U/preparation) and stored at -80°C. The concentration and purity of the RNA will be determined by measurement of the absorbance at 260 and 280nm and RNA 6000 Nano assay (Agilent Technologies) according to manufacturer’s instructions.

**Micro array analysis of global gene expression**

Affymetrix Gene Chip array expression profiling will carried out using the facilities at the John Innes Genome Lab, [http://www.jicgenomelab.co.uk](http://www.jicgenomelab.co.uk/). All protocols described can be found in the Affymetrix Expression Analysis Technical Manual II (Affymetrix Manual II) <http://www.affymetrix.com/support/technical/manuals.affx>. Briefly, first strand cDNA synthesis will performed according to the Affymetrix Manual II, using 5g of total RNA. Second strand cDNA synthesis will be performed with minor modifications to the Affymetrix Manual II, double-stranded cDNA products will be immediately purified following the “Phase Lock Gel Cleanup of Double-Stranded cDNA” protocol and then the cDNA will be re-suspended in 22L of RNAse free water.

cRNA preparation will be performed with minor modifications to the Affymetrix Manual II. Briefly, 11uL of cDNA will be used as a template to produce biotinylated cRNA using half the recommended volumes of the ENZO BioArray High Yield RNA Transcript Labelling Kit. Labelled cRNAs will be purified following the “Qiagen RNeasy Cleanup and Quantification of Biotin-Labelled cRNA” protocol (Affymetrix Manual II). cRNA quality will be assessed using Agilent RNA6000nano LabChips® (Agilent Technology 2100 Bioanalyzer Version A.01.20 SI211). cRNA quantity will be assessed by running 1l of each cRNA sample on a NanoDrop® ND-1000 UV-Vis Spectrophotometer (Nanodrop Technologies). 20µg of cRNA will be fragmented and hybridisation cocktails will be setup according to the Affymetrix Manual II.

High-density oligonucleotide arrays containing probes of more than 22000 different human genes (human U133A arrays, Affymetrix, Santa Clara, CA) will be used for gene expression detection. Hybridization overnight at 45oC and 60RPM (Hybridization Oven 640), washing and staining (GeneChip® Fluidics Station 450, using the EukGEws2_450 Antibody amplification protocol) and scanning (GeneArray® 3000) will carried out according to the Affymetrix Manual II. CGOS (Affymetrix) will be used for image analysis and to determine probe signal levels. The average intensity of all probe sets will be used for normalization and scaled to 100 in the absolute analysis for each probe array. Data from GCOS will then be analysed in GeneSpring® software version 6.0 (Silicon Genetics, Redwood City, CA).

**Analysis of Key Se-responsive genes - RT-PCR**

**(TaqMan analysis)**

Determination of mRNA levels of key selenium responsive genes will be performed using real-time RT-PCR (TaqMan assay). Fluorogenic probes with 5’ FAM (6-carboxyfluoroscein) reporter dye and 3’ TAMRA (6-carboxytetramethylrhodamine) quencher dye will be used to target key selenium responsive genes, which may include (SepW1, SelP, Casp10, IL10, IGF1R, TNFS14, CD1D). RT-PCR reactions will be performed in 96 well plates using TaqMan one-step RT-PCR master mix reagent kit (Applied Biosystems) in a total volume of 25 µL/well consisting of 100nM probe, 200-300nM forward and reverse primers and 10ng RNA. TaqMan RT-PCR conditions: 48°C 30 min, 95°C 10 min then 40 cycles of 95°C for 15 s and 60°C for 1 min. TaqMan threshold cycle number (Ct) will be normalized into fold of relative induction using the equation of ∆Ct method, fold of induction = 2Ct(control) – Ct(treatment). Standard curves will be constructed using total RNA in triplicate to provide a range which encompasses the range of observed sample values.

**6.62ii** Blood: **Cellular and Humoral Immune Response**

**NK- and CD8-mediated cell cytotoxicity**

NK and cytotoxic T cells (effector cells) will be isolated by negative selection. Target cell membranes will be labelled with a fluorescent carbocyanin dye. Effector and Target cells will be mixed together to allow cytotoxic reactions to occur. Propidium Iodide will then be added to this mixture to assess cell death. Quantification beads will be added at the same time. The first set of data will be acquired by flow cytometry to give an absolute viability count. The same cells will then be washed, fixed and permeabilised to allow detection of intracellular antigens after staining with fluorochrome-labelled phenotypic markers and antibodies to perforin and granzyme contained within the Effector cells. After washing the cells data will be acquired by flow cytometry.

**In vitro analysis of cytokines production**

Mononuclear cells will be isolated from peripheral blood by density gradient centrifugation and cultured under standard conditions in the presence or absence of influenza antigens. Supernatants will be collected and stored -20°C for later analyses of cytokine content. Secreted cytokines will be measured using bead array technology and according to manufacturer’s instructions. Data will be acquired by flow cytometry. A variant of this method will be used to detect levels of IFNγ. In such a case a protein transport inhibitor will be added 4 hours before termination of culture, after which cells will be washed, permeabilised and stained for intracellular cytokine and phenotype. Data will be acquired by flow cytometry.

**Tissue culture and bi-parametric DNA/BrdU analysis for flu-specific proliferative response**

Standard methods require the inclusion of a control antigen, i.e. polio-virus antigen. In order to develop this assay a prescription for obtaining the commercially available poliomyelitis vaccine (inactivated) will be sought from one of the IFR medical advisor.T-cells will be cultured in the presence or absence of influenza and polio antigens, according to standard methods. Bromodeoxyuridine (BrDU) will be added shortly before the end of the culture period. After a further incubation, BrDU-pulsed cells will be stained with fluorochrome-labelled antibodies for their phenotypic identification. These cells will then be washed, fixed, permeabilised and subject to DNAase treatment to expose incorporated BrDU before staining with fluorochrome-labelled anti-BrDU antibody. At this time cells may also be stained with other antibodies for detection of relevant intracellular proteins. Total DNA will be identified with a DNA-specific dye. All data will be acquired by flow cytometry.

**Isotype-specific antibody titres by ELISA**

96-well immunoplates will be coated with the antigen at 4C overnight, and then plates will be incubated with blocking solution (10%BSA in PBS) and then washed. Serum samples are then added in triplicate at appropriate dilutions. Samples of previously defined positive control sera and appropriate negative controls are run in each plate. Plates are incubated at room temperature for 1h and washed carefully. This is step is the followed by the incubation with unlabelled antibody specific to human isotype (IgA, IgG1 and IgG3) and then by incubation with peroxidase conjugated anti-mouse IgG. After washing, 200uL of the chromogenic substrate TMB are added to the wells. Reaction is stopped by addiction of acid, and the colour developed is read at 450nm using a microplate reader.

**Analysis of expression and distribution of NF-kB**

Expression and intracellular distribution of NF-B and its inhibitor I-B will be evaluated by flow cytometry. After a recall challenge *in vitro* with influenza vaccine cells will be fixed and permeabilized using appropriate commercially available solution (Fix and Perm, Caltag, Medsystem Ltd) and then stained with specific anti-NF-B and anti-IB antibodies. A mixture of fluorescently labelled (PE or Cy5) respectively will be then added. The samples will be then stained with propidium iodide and analysed by flow cytometry.

### 6.64 Saliva Samples: Humoral Response

**Detection of individual antibody forming cells by Enzyme linked immunospot (ELISPOT)**

Nitrocellulose filters will be coated with the appropriate dilution of viral protein or control antigen diluted in phosphate buffer saline. After incubation at 4oC overnight, plates are washed 3x with 300µL PBS-T per well. Background controls consisting in wells incubated under the same conditions but with PBS only are included in each plate. Plates are blocked with 200µL /well of complete medium for 30min-1h at 37oC and rinsed in PBS. This is followed by incubation with lymphocytes at different concentration for 4-6 hours at 37oC. Individual antibody forming cells (AFC) will be then detected by the addition of enzyme-labelled antibodies specific for different isotypes (IgA/G/M) Immunospots will be by the addiction of appropriated enzyme (alkaline phosphatase or HRP)-labelled antibody. Immunospot will then visualised by the addition of the appropriate enzyme colour development reagents. The substrate reaction will be stopped by rinsing and filters will be air-dried the spots enumerated either automatically or manually by inspection under dissecting microscope.

**Isotype-specific antibody titres by ELISA**

96-well immunoplates will be coated with the antigen at 4C overnight, and then plates will be incubated with blocking solution (10%BSA in PBS) and then washed. Saliva samples are then added in triplicate at appropriate dilutions. Samples of previously defined positive control sera and appropriate negative controls are run in each plate. Plates are incubated at room temperature for 1h and washed carefully. This is step is the followed by the incubation with unlabelled antibody specific to human isotype (IgA, IgG1 and IgG3) and then by incubation with peroxidase conjugated anti-mouse IgG. After washing, 200uL of the chromogenic substrate TMB are added to the wells. Reaction is stopped by addiction of acid, and the colour developed is read at 450nm using a microplate reader.

**6.65 Determination of alpha-tocopherol in serum**

Plasma carotenoids, retinol, and -tocopherol will be assayed with a modified HPLC technique as descried by Hughes et al (1997). Duplicate aliquots (500l) of freshly thawed plasma will be added to aqueous sodium dodecyl sulphate (lysing agent; 500l; 10mmol/L), and retinol, -tocopherol, and the carotenoids will be extracted simultaneously into two 3ml portions of hexane. The combined extracts will be dried under nitrogen and redissolved in dichloromethane and mobile phase mixture at a ratio of 1:9 (vol/vol) before HPLC analysis as described by Fuller et al (1992). Retinol, -tocopherol, and the carotenoids will be determined simultaneously by monitoring the HPLC column eluent at 328nm (retinol) for the first 5 minutes of the run and at 297nm (-tocopherol) for the following 10 minutes. Standard solutions for retinol and -tocopherol will be combined with the mixed carotenoid working standard to give final concentrations of 2.5mg/L retinol and 100mg/L -tocopherol.

# 7.0 Statistical Analysis

Power calculations were done so that, out of the six study groups, a difference of 1 standard deviation in response variable between the minimum and maximum responding groups would be reliably detected. For example, for plasma selenium, previous studies (Shortt et al, 1997) suggest that the population standard deviation is 11.7, and so our sample sizes are designed to give an 80% chance of detecting a range of plasma selenium between the six groups of 11.7. For antibody secreting cells/500,000 lymphocytes and specific serum antibody (both at day 7 post-vaccination) the corresponding standard deviations are 76 and 19 respectively (Cox et al, 1999).

The power calculations also assumed that any effect of selenium supplementation would be proportional to the amount of supplementation, with enriched onions being equivalent to a supplementation of 50µg/day selenium and the un-enriched onions equivalent to no supplementation.

The power calculations were also based on the assumption that the data would be analysed using a one-way ANOVA model, the grouping having six levels (control, 50µg/day selenium, 100µg/day selenium, 200µg/day selenium, enriched onions, non-enriched onions). In order to be able to detect a range of 1 standard deviation between the groups with a power of 80%, a sample size of 144 (or 24 in each group) is sufficient. This allows for a drop-out rate of 25%, or in other words, finishing with 18 subjects in each group.

In the unlikely event of there being a year effect, and thus the two onion groups (but not the control and supplementation groups) being potentially compromised,24 subjects in each of the remaining 4 groups gives a power of 80% of detecting a range of 1 standard deviation in the response variable. This is based on using a two-way ANOVA model to analyse the data, with a three level year effect and a four level group effect (control, 50µg/d Se, 100µg/d Se, 200µg/d Se). It is important to stress however that we are aiming to recruit the full complement of 24 volunteers without the drop out rate of 25% as we feel there is a greater chance of compliance with the supplementation intervention.

In order to allow for the unlikely possibility of a year effect the control group and each of the three selenium supplementation groups will be evenly and randomly spread over the three years. Unfortunately due to time constraints, this is not possible with the onion groups which will be evenly and randomly spread over only two of the years (i.e. half in each year). The two onion groups will also be able to be analysed separately, but with a reduced power of 18 subjects per group gives a power of 80% of detecting a difference in response variable of 1 standard deviation. This is quite a large effect of the enriched onions, given that they are only “equivalent” to a selenium dose of 50µg/day. This is based on a 25% drop out rate expected for the onion intervention study.

The data would be initially analysed using an ANOVA model to test for differences in end-points between the groups. If the required data assumptions for this model are not met (e.g. normality), then data transformations and/or non-parametric methods will be employed. A repeated measures analysis using all 5 data points per subject will also be used, although it is the end-point (week 12) that is of primary interest.

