## 6.0 Study Protocol

## Due to the nature of the study (onions only available in year 2 and 3) and the fact that some volunteers may have a dislike or intolerance to onions it would be difficult to fully randomise the study and unethical to accept those volunteers onto the onion part of the study. In year 2 and 3, which includes the onion, intervention, volunteers with no dislike of onions will be randomly allocated to one of six groups.  Volunteers with a dislike of onions will be randomly allocated to one of four groups.  There is no evidence to suggest that volunteers who do not or cannot eat onions will display any differences in immune function response or selenium status to those volunteers that do, and thus there will be no consequences of the study not being fully randomised.  However, as this is a new area of research, the preferences of all subjects recruited in the first year of the study will be monitored, and the possibility of differences by onion “preferences” investigated.

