## 6.4 Volunteer Randomisation

Ideally the study would be completely randomised, but this would compromise our ability to complete recruitment in the time allowed i.e. only accepting volunteers onto the study that like onions so that they could be randomised into any one of six groups (years 2 and 3 only as year one is the supplement study only). It would also beunethical to accept volunteers who had a dislike or intolerance to onions onto the onion part of the study.  Volunteers will as far as possible be randomly allocated to one of four groups in year one (0µg/day (placebo), 50µg/day, 100µg/day and 200µg/day of Se-yeast) and one of six groups in years 2 and 3 (the selenium supplements above as well as selenium-enriched and un-enriched onion groups).  There is no evidence to suggest that volunteers who do not or cannot eat onions will display any differences in immune function response or selenium status to those volunteers that do, and thus there will be no consequences of the study not being fully randomised.  However, as this is a new area of research, the preferences of all subjects recruited in the first year of the study will be monitored, and the possibility of differences by onion “preferences” investigated. Volunteers will be stratified by sex. The volunteer information document (annex 4) will clearly state that volunteers recruited in 2005 will be assigned to the supplement study only.

|  | Volunteers to be recruited | | |
| --- | --- | --- | --- |
|  | Selenium-enriched onions | Un-enriched onions | Selenium-Supplementation |
| Year 1 (2005-2006) | n=0 | n=0 | n=32 |
| Year 2 (2006-2007) | n=12 | n=12 | n=32 |
| Year 3 (2007-2008) | n=12 | n=12 | n=32 |

Table 1: Study groups outlined

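### Onion-versus-tablet contrasts and the six-group test are open to confounding by year and onion preference; the named ANOVA has no term for either, and the year contingency drops the onion groups

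*Protocol*

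**What the plan says.** Section 7.0 sizes the trial so that "a difference of 1 standard deviation in response variable between the minimum and maximum responding groups would be reliably detected", citing plasma selenium as an example, for which "the population standard deviation is 11.7". The calculation assumes that "the data would be analysed using a one-way ANOVA model, the grouping having six levels". The analysis sentence later in the section is less specific: "The data would be initially analysed using an ANOVA model to test for differences in end-points between the groups".

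Allocation is not the same for everyone. Section 6.0 states: "Volunteers with a dislike of onions will be randomly allocated to one of four groups". Other volunteers in years 2 and 3 can enter any of six groups. Table 1 and section 7.0 spread the tablet groups evenly over three years, but describe the "onion groups which will be evenly and randomly spread over only two of the years". Volunteers are stratified by sex (sections 6.1 and 6.4).

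Section 6.4 concludes that "there will be no consequences of the study not being fully randomised", while undertaking to monitor preferences in year-1 recruits and look for differences. Section 7.0 does foresee trouble from year. The paragraph that begins "In the unlikely event of there being a year effect, and thus the two onion groups" accepts that those groups could be affected, and falls back on a two-way ANOVA with year in the four tablet groups. The two onion groups may then be analysed on their own.

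**The concern.** Year and onion preference decide who can enter an onion group. A model with group alone therefore attributes any outcome difference between year 1 and later years, or between people who accept and dislike onions, to the onion-versus-tablet contrast. The first objective in section 3.0 concerns two organic forms of selenium, and the direct comparison of the forms at 50 µg/day is enriched onions against the 50 µg tablet. The contingency does not repair that comparison. It abandons it, although years 2 and 3 contain all six groups and so allow it to be estimated with year in the model.

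The statement that incomplete randomisation has no consequences is argued only for preference, and only from absence of evidence. Section 6.0 gives two reasons for incomplete randomisation, preference and the missing year-1 onions, and section 7.0 concedes that the second could matter.

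**Working it through.** **Inputs.** From Table 1 and section 7.0: each tablet group has 8, 8 and 8 volunteers in years 1 to 3; each onion group has 0, 12 and 12. With 25% drop-out, 24 per group becomes 18. Under the protocol's dose-proportional assumption the group means, in SD, are 0, 0.25, 0.5, 1 (placebo, 50, 100, 200 µg), 0.25 (enriched) and 0 (un-enriched). Assumed, because the protocol gives no value: two-sided alpha 0.05, the size of any year or preference effect, and the share who dislike onions.

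**The plan's own figure.** The mean of the six values is 2/6 = 0.333, and the sum of squared deviations is 1.375 − 6 × 0.333² = 0.708. At 18 per group the non-centrality is 18 × 0.708 = 12.75. The large-sample chi-square test on 5 df gives 79.7%, which matches the stated 80%. The exact F-test gives 77.2%, or 89.7% at 24 per group.

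**Bias from year.** With year effects y1, y2, y3, the unadjusted onion-minus-tablet difference carries

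(y2 + y3)/2 − (y1 + y2 + y3)/3 = −(1/3) × [y1 − (y2 + y3)/2].

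A year-1 shift of d against the later years therefore gives a bias of d/3 in size. Simulated rejection by the one-way six-group test with no treatment effect (20,000 runs):

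| Year-1 shift (SD) | Bias (SD) | 18 per group | 24 per group |
|---|---|---|---|
| 0.5 | 0.17 | 7.2% | 7.9% |
| 0.75 | 0.25 | 8.9% | 11.4% |
| 1.0 | 0.33 | 12.5% | 17.0% |

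Repeat runs agreed to within about 1 point. With year in the model, rejection was 4.9 to 5.3%. For scale, 0.25 SD is the whole effect that the plan assumes for enriched onions.

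**Bias from preference.** Suppose 20% of recruits dislike onions. In years 2 and 3 they all fall among the 32 tablet places out of 56, so their share there is 0.20 × 56/32 = 35%. Over three years the tablet share is (8 × 0.20 + 16 × 0.35)/24 = 30%, against 0% in the onion groups (15% if 10% dislike onions). A preference effect of 0.5 SD gives a bias of 0.30 × 0.5 = 0.15 SD, and null rejection at 24 per group is 8.7%. With year and preference effects both 0.5 SD and acting in the same direction, the simulated bias is 0.33 SD and null rejection 21.5%.

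**The preference check.** With 32 year-1 volunteers and 20% dislikers, the comparison is 6.4 against 25.6, with SE √(1/6.4 + 1/25.6) = 0.44 SD. Multiplied by about 2.9 for 80% power, the detectable difference is about 1.3 SD (1.1 to 1.7 SD for 30% to 10% dislikers). The check could miss effects large enough to matter.

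**What is not affected.** The two onion groups share one year and preference make-up, and the four tablet groups share another, so contrasts within each set are unbiased. Sex effects of 0.5 and 1 SD gave no bias; the unadjusted test became conservative (4.0% and 1.6% rejection).

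**After adjustment** for year, preference and sex, bias was zero within simulation error and rejection 4.5 to 5.6%.

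| Model (10 to 20% dislikers) | Power, 18 per group | Power, 24 per group | SE of enriched − 50 µg, 24 per group |
|---|---|---|---|
| Group | 77.2% | 89.7% | 0.289 |
| + year | 75.8% | 88.8% | 0.298 |
| + year, preference, sex | 75.3 to 74.6% | 88.4 to 87.9% | 0.302 to 0.308 |

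The variance cost of the full model is (0.302/0.289)² = 1.09 to (0.308/0.289)² = 1.14.

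**The case against.** The strongest reply is that each form of selenium has its own blinded, concurrent control. Enriched minus un-enriched and 50 µg tablet minus placebo are both unbiased, and their difference compares the forms without a year term. That is correct, and it means the first objective does not depend wholly on the direct contrast. But the protocol does not name that difference. It needs the same additivity as an adjusted model, and its variance is 4/24 against 2/24 for the direct contrast, so double rather than 9 to 14% higher. The six-group omnibus test stays exposed either way. It also stands that a direct onion-versus-tablet difference mixes meals with tablets, which no stratum term removes.

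Second, the one-way wording is an assumption of the power calculation, the analysis sentence says only an ANOVA between groups, and a statistical analysis plan (not available here) may add terms. A reader might infer that the protocol fixes a one-way primary model; it does not. What it does fix is the no-consequences statement and a contingency that removes the onion groups from the joint analysis. A later plan that added strata would have to override both.

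Third, a reader might infer that year is ignored. It is not: tablet groups are balanced over years and a year model is foreseen for them. A reader might also count sex as a third confounder because allocation is stratified by it. Stratification balances sex across groups, so leaving it out costs precision only.

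Last, the protocol calls a year effect unlikely and knows of no preference effect. Nothing in it shows otherwise; at a 0.25 SD shift the bias is only 0.08 SD and rejection about 6%. Still, section 6.1 allows vaccination in March and April 2007 and 2008, in years 2 and 3 but not year 1, if deliveries require it. The years may therefore differ in vaccination timing.

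**Conclusion.** The concern holds for direct onion-versus-tablet contrasts and for the six-group omnibus test. Followed as written, the plan either leaves them open to confounding by year and onion preference or gives up the onion-versus-tablet comparison. The bias is one third of any year-1 shift, plus about 0.15 to 0.30 of any preference effect if 10 to 20% dislike onions. A 1 SD year-1 shift raises null rejection to about 12% (18 per group) or 17% (24 per group).

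These sizes rest on assumed shifts and an assumed dislike share. Confounding is possible, not demonstrated. The documents do not support extending the point to contrasts within the onion pair or among the tablet groups, or to sex. Adjustment removes the bias only if stratum effects are additive. This is a cheap improvement rather than a fatal flaw.

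**What to change.** In section 7.0, state that end-points in all six groups are analysed with group, year and recorded onion preference, plus sex for precision, whether or not a year effect is found. Define the preference stratum by each volunteer's recorded preference, including in year 1, when everyone is randomised to four groups and eligibility alone would not separate people.

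As a check that does not rely on additivity across strata, repeat the onion-versus-tablet contrasts in onion-accepting volunteers randomised in years 2 and 3. This check is less precise. With 10 to 20% dislikers, about 16 × 0.825 = 13.2 to 16 × 0.65 = 10.4 volunteers remain per tablet group, and the SE is √(1/24 + 1/13.2) = 0.34 to √(1/24 + 1/10.4) = 0.37 SD.

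Replace the no-consequences statement in sections 6.0 and 6.4 with an account of how year and preference are handled, and replace the contingency that takes the onion groups out of the joint analysis.

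No new recruitment is needed. Year and sex are known; preference determines allocation in years 2 and 3 and is already to be monitored in year 1. The cost is about 1 point of power for year alone. With preference and sex added it is about 2 to 3 points at 18 per group, and 9 to 14% more variance on the onion-versus-tablet contrast.
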